Patients will discontinue all pain medications (opioids, NSAIDS, anti-depressants and anti-convulsant drugs), supplements, chondroprotective drugs, and other alternative therapies for KOA for 10 days prior to the screening/baseline visit. During follow-up, patients will be prohibited from undergoing any other adjunctive treatment for KOA, including steroid injections, viscosupplementation, and pain medications. Serious local complications from either CRFA or CRYO and the need for medications for pain relief will be a criterion for study discontinuity.

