### Sample size

According to the protocol, the patients will be randomly assigned into two groups, and they will all be evaluated (with NPRS) four more times after the baseline assessment (15 days, 4 weeks, 12 weeks, and 24 weeks, post-intervention). The main objective is to examine the possible diversity in NPRS (primary outcome) improvement among patients in different groups. The regular statistical approach to do this is to perform repeated measures ANOVA (rmANOVA), taking as given that all ANOVA assumptions are met (for example, normality of scores). Thus, the statistical power analysis for an rmANOVA procedure is as follows: we, as a priori, assume a number of groups equal to two and a number of measurements (except baseline) equal to four. More specifically, the NPRS is expected to be reduced in the two groups (CRYO and CRFA) at least 30%, relative to baseline assessment. According to Cohen [35], this fact denotes a medium effect size of approximately 0.50. Statistical significance is usually considered at the 5% level, and the power analysis curve for the rmANOVA is shown in Fig. 3. This figure illustrates that approximately 47 patients suffice for an achieved power of 80% using rmANOVA, taking into account a moderate effect size and 62 patients for 90% statistical power. Considering a 10% loss of follow up, we will enroll 70 patients in the study.

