### Data collection and management

Data will be collected in paper forms at baseline and 2-, 4-, 12-, and 24-weeks post-intervention. Quality assessments and proper training sessions will be conducted to ensure that all information is collected properly. Outcome data include the NPRS, KOOS, OKS, and PGIC, all of which are patient-reported questionnaires. Demographic data, radiographs (downloaded from PACS and saved in JPEG format), and intraoperative pictures of skin marks or videos from the interventions will also be collected. A hard copy folder will be created for each patient, including all paper forms, demographic data, and intervention details. These folders will be kept safe in the hospital office of the primary investigator ([name]) inside a special locker. The other main investigator ([name]) will transfer all the data into an Excel database using the desktop computer at the office of the primary investigator ([name]). Patient identification will be performed using only the national insurance number (11-digit number). Excel forms without patient names will be used for data analysis. Paper forms and computerized data could be assessed only by the two primary investigators. These files will be kept for at least three years after the last enrolled patient for future expansion of the research. We are not expecting participants to discontinue or deviate from the primary intervention. The coordinator nurse will be responsible for contacting them for missing appointments of clinical evaluation, either by phone or email. In case of refusal to attend, we plan to send the questionnaires by mail or make home visits. No other efforts will be made to minimize the loss of follow-up. Missing data from more than one time point will be a reason for dropout from the study.

Data entry, coding, security, storage, assessment of quality and creation of Excel tables will be under the responsibility of the two main investigators. Excel database would be password-protected. Personal information about potential and enrolled participants before, during, and after the trial will be collected to ensure confidentiality (using only the national insurance number as an indicator).

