### Statistical methods

The sample size and power in the study have been previously described. Another statistical approach for the study is to evaluate all follow-up (post-intervention) measurements separately from the baseline. This may occur in two possible ways: one with the use of an ANCOVA procedure and the other with the use of ANOVA on the difference in the scores (follow-up minus the baseline). As Borm et al. [36] suggested, the ANCOVA approach requires a significantly smaller number of participants, reduced by a multiplicative factor that depends on the correlation estimate between the prior and posterior scores, which is usually high. More specifically, a significance level of 5% along with a power of 80% is achieved with 24–45 patients in total, when the correlation estimates between the a priori and a posteriori score is approximately 80–90%, which is a realistic approach. To sum up with the statistical plan, longitudinal (that is, repeated measures) analysis will be conducted with repeated measures ANOVA. Furthermore, the slopes of the score trajectories (trendlines) will be compared among the two patient groups using 1-way ANOVA. Bivariate comparisons for baseline versus follow-up will be conducted using ANCOVA. 1-way ANOVA will assist in detecting variations in bivariate differences of scores (baseline versus each follow-up) among the two patient groups. Data will be reported as differences between group means (means ± standard deviations, 95% CIs) if normal distributed, otherwise as medians with interquartile ranges. Categorical data will be reported as numbers and proportions. A statistically significant difference of at least two in NPRS scores between groups, will be interpreted as a minimal clinically important difference (MCID). The statistical method of pairwise (available case analysis—ACA) deletion will be used for missing data at only one time point. If more than two time points are missed the list-wise (Complete-case analysis—CCA) deletion method will be used. Statistical analysis will be performed using R language and Rstudio IDE, two well-known open-source products.

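### The missing-data rules leave exactly two missed visits without an analysis rule, do not fit the repeated-measures ANOVA, and rely on deletion although discontinuation is tied to pain

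*Protocol article*

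**What the plan says.** Three parts of the protocol article bear on missing pain scores.

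- **Data collection and management** sets a rule on study status: "Missing data from more than one time point will be a reason for dropout from the study". It also describes retention efforts: "In case of refusal to attend, we plan to send the questionnaires by mail or make home visits".
- **Statistical methods** sets rules for analysis. Pairwise (available-case) "deletion will be used for missing data at only one time point". Then: "If more than two time points are missed the list-wise" (complete-case) deletion applies. The same section states that "longitudinal (that is, repeated measures) analysis will be conducted with repeated measures ANOVA". It adds ANCOVA and one-way ANOVA of change at each follow-up, and a comparison of slopes.
- **The last paragraph under CRYO technique**, which covers both arms, says that "the need for medications for pain relief will be a criterion for study discontinuity". Serious local complications are the other criterion.

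The Sample size section powers the trial on the repeated-measures ANOVA, with a "number of groups equal to two and a number of measurements (except baseline) equal to four". It gives about 47 patients for 80% power and 62 for 90%, and raises the number to 70 for 10% loss to follow-up.

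**The concern.** There are three linked problems.

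1. **The thresholds differ.** One section acts at more than one missed time point, the other at one and at more than two. Exactly two missed visits falls between them. With visits at weeks 2, 4, 12 and 24, this is the pattern of a patient who leaves between weeks 4 and 12. Whether that patient's first two scores count is left open and could be settled after the data are seen.
2. **The deletion rule does not fit the model.** Standard repeated-measures ANOVA needs a score at every occasion. A patient with one gap leaves it, whatever the pairwise rule says. In the visit-by-visit tests pairwise deletion works, but the patients compared can then change from visit to visit.
3. **Missingness can depend on pain.** If patients who need analgesics leave the study, deletion removes treatment failures. The retained patients then look better than the randomised ones.

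At stake are the size of improvement from baseline, which is the trial's main hypothesis, and the comparison between arms if the two arms lose failures at different rates.

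**Working it through.** **Rules side by side, by number of missed follow-up visits**

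| Missed | Data collection and management | Statistical methods |
|---|---|---|
| 1 | stays in the study | pairwise deletion |
| 2 | dropout | no rule |
| 3 or 4 | dropout | list-wise deletion |

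The sections diverge only in the middle row.

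**The plan's own numbers.** Inputs from Sample size: two groups, effect size 0.50, 5% level. The article does not say which effect-size measure is meant; I took it as Cohen's f. For the within-patient or group-by-time effect under sphericity I used a noncentral F with noncentrality f²N, numerator df m − 1 and denominator df (N − 2)(m − 1).

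- m = 5 occasions (baseline plus four): N = 49 for 80% power and 63 for 90%; power 0.781 at 47 and 0.896 at 62.
- m = 4 occasions: N = 45 and 59; power 0.820 at 47 and 0.920 at 62.
- Loss to follow-up: 62 / 0.9 = 68.9, so 69; the plan's 70 gives 35 per arm.

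The stated 47 and 62 lie between the two variants, so I do not dispute them.

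**Evaluable number**

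- Planned loss: 70 × 0.9 = 63, at or above the stated 62 (power 0.90 to 0.93).
- No per-visit rate is given. Assume each of four visits is missed independently with probability p, so that 70 × (1 − p)⁴ patients have all four scores:
  - p = 3%: 70 × 0.885 = 62
  - p = 5%: 70 × 0.815 = 57 (power 0.87 to 0.89)
  - p = 8%: 70 × 0.716 = 50
- At the other extreme, if the same patients miss every visit, 5% to 8% leaves 70 × 0.95 = 66.5 to 70 × 0.92 = 64.4.

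**Selection bias (illustration, assumed figures).** Suppose m of an arm's 35 patients are deleted and their mean NPRS is k points worse than that of the retained patients. The full-arm mean is then the retained mean plus m × k / 35. Improvement is overstated by m × k / 35 in that arm, and the between-arm difference shifts by (m₁ − m₂) × k / 35. With the planned 7 losses and k from 2 to 4:

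- Even split (3.5 each on average): 3.5 × 2 / 35 = 0.20 to 3.5 × 4 / 35 = 0.40 points of overstated improvement in each arm; no shift in the difference.
- 5:2 split: 3 × 2 / 35 = 0.17 to 3 × 4 / 35 = 0.34 points of shift.
- 7:0 split: 7 × 2 / 35 = 0.40 to 7 × 4 / 35 = 0.80 points of shift.

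The protocol's threshold for a clinically important difference between groups is 2 points.

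**The case against.** The two sections do different jobs, one setting study status and the other analysis. They agree in effect for one missed visit and for three or four. A reader might infer that the rules contradict each other throughout; the text does not support that.

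The pairwise rule is the milder one, since it keeps a patient's observed visits. It is coherent for the ANCOVA and change-score tests, and the article does not say which analysis it serves. This stands. The misfit is with the repeated-measures ANOVA alone, but that is the analysis on which the trial is powered.

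Baseline-adjusted ANCOVA tolerates missingness that depends on arm and baseline pain. This also stands, but it does not cover missingness that depends on pain after treatment, which is what the discontinuation criterion can produce.

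Mailed questionnaires and home visits should limit missed appointments. The article does not say that they extend to patients discontinued for needing analgesics.

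A reader might also infer that the evaluable number will fall below 62. The planned loss leaves 63, the 5% to 8% per-visit rates are my assumption, and independence is unfavourable to the plan because clustered gaps leave more complete patients. Even 50 to 57 exceeds the 47 stated for 80% power.

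Finally, one might read the dropout rule as discarding scores already collected. The article says only that such a patient leaves the study and is silent on the earlier scores.

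**Conclusion.** The point holds in a limited form. The gap at exactly two missed visits, and the misfit between deletion and the repeated-measures ANOVA, are plain in the text. The main risk is selection. If patients whose pain returns are the ones lost, deletion overstates improvement in each arm that loses them. The comparison is biased only if such loss differs between arms, and then towards the arm losing more non-responders. The documents give no basis for saying which arm that would be, or that it will happen. On the assumed figures the shift is 0.17 to 0.34 points for a 5:2 split and at most 0.80 for the extreme 7:0 split, so it is modest against the 2-point threshold. Loss of 90% power is secondary and depends on per-visit rates that the plan does not give. The plan should be changed, but the point does not call the design or the sample size into question.

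**What to change.** Replace the pairwise and list-wise rules in Statistical methods, and the dropout sentence in Data collection and management as far as it affects analysis, with one rule:

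- Analyse patients in the arm allocated and keep every observed NPRS score, whatever the number of missed visits.
- Use a likelihood-based mixed model for repeated measures with baseline NPRS as covariate. It uses partial records and is valid if data are missing at random.
- Report by arm any randomised patient with no post-baseline score, because requiring one such score is close to, but not the same as, analysing everyone randomised.
- Add one delta-adjusted sensitivity analysis that worsens missing scores by an amount fixed in advance, since missing at random may fail when pain drives discontinuation.

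Reconcile these two sections with the discontinuation criterion under CRYO technique, so that the plan states whether scores collected before discontinuation are kept. No change to the clinical criterion is proposed.

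The cost is wording, one further analysis and a little programming in R, which the plan already names. Sample size and visits stay as they are. The change should be dated before any comparison by arm, including the planned interim analysis.

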### Interim and additional analyses

Interim analyses will be performed when at least half of the CRFA and CRYO patients have been recruited; reasons for discontinuance would be serious complications or significant differences in clinical outcomes (especially for CRYO, which is a new approach not thoroughly tested so far). Although the sample size is small, we plan to perform additional subgroup analyses for age, sex, arthritis stage, and deformity type (varus or valgus).

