### Randomization—sequence generation

A total of 70 patients will be included in the study (CRFA:35; CRYO:35) Randomization sequence will be created using Stata 9.0 (StataCorp, College Station, TX) statistical software and will be stratified with a 1:1 allocation ratio using random block sizes of 2, 4, and 6. An investigator not involved in the main study ([name]) will perform the randomization process. These data will be stored on computer and will be available at the day of the intervention.

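### The interim look is triggered by recruitment, yet it may stop the trial on undefined outcome differences, at a time when almost no patient has 24-week pain scores

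*Protocol article*

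**What the plan says.** Under Interim and additional analyses, the protocol article fixes the timing: "Interim analyses will be performed when at least half of the CRFA and CRYO patients have been recruited". It then gives two grounds for ending the trial, joined by an or: "reasons for discontinuance would be serious complications or significant differences in clinical outcomes". A parenthesis adds that this applies particularly to CRYO, as a new and little-tested approach. The section does not say which outcome, which visit, what size of difference or what p-value would count, or how many looks there will be.

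Under Sample size, the level appears once, in general terms: "Statistical significance is usually considered at the 5% level". The calculation assumes "a number of groups equal to two and a number of measurements (except baseline) equal to four", and concludes: "Considering a 10% loss of follow up, we will enroll 70 patients in the study". Statistical methods repeats 5% for an alternative ANCOVA calculation and names repeated measures ANOVA as the longitudinal analysis. Neither section mentions an interim look.

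Under Outcomes, the primary NPRS outcome is taken at 2, 4, 12 and 24 weeks. Under Recruitment, 70 patients are expected in 10–12 months.

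**The concern.** Two things do not fit together. First, the trigger counts patients recruited, while one of the two stopping grounds depends on outcomes that take up to 24 weeks to collect. A recruitment trigger suits complications, which are recorded from the procedure onward. It does not suit an efficacy comparison whose aim is set at six months.

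Second, the outcome-based ground has no criterion. If it is applied as an ordinary significance test and the final test is also run at 5%, the trial has two chances of a false positive, or more if several visits or scales can trigger the stop.

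The timing matters particularly for this comparison. The introduction and the limitations section describe the two techniques as differing in nerve regeneration and permanence of damage, so their pain curves may differ in duration. A stop driven by the first weeks would end recruitment before that question could be answered at the planned size.

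**Working it through.** **1. The plan's own sample size.** Inputs: 62 patients for 90% power and 10% loss (Sample size). 62 / (1 − 0.10) = 68.9, so 69; the plan rounds to 70. As a check on the 62, a noncentral F calculation for a within-patient or interaction effect with a single final analysis, f = 0.5, noncentrality f² × N and five measurements gives 49 and 63 patients for 80% and 90% power. With four measurements it gives 45 and 59. The stated 47 and 62 lie between these, so they look like fixed-design figures with nothing added for an interim look. The type of effect size is not stated, so this match is only indicative.

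**2. Data available at the trigger.** Assumptions: even accrual, look at the 35th patient, time counted from treatment.
- Recruitment period: 10 months = 10 × 365.25 / 12 / 7 = 43.5 weeks; 12 months = 52.2 weeks.
- Half recruitment, H: 21.7 or 26.1 weeks.
- Patients past visit w: 35 × (H − w) / H, or 0 if H < w.

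| Visit | 10 months | 12 months |
|---|---|---|
| 2 weeks | 31.8 | 32.3 |
| 4 weeks | 28.6 | 29.6 |
| 12 weeks | 15.7 | 18.9 |
| 24 weeks | 0 | 2.8 |

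In whole patients, allowing for rounding, this is about 0–3 with 24-week scores, 15–19 with 12-week and 28–30 with 4-week. If recruitment is counted from the screening visit three weeks before treatment (Table 1), the 24-week count is 0 in both cases.

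**3. Type I error, one endpoint.** Assumption: the look uses two-sided p<0.05 at information fraction t, and so does the final test. The two z statistics are bivariate normal with correlation √t. The overall error is 1 − P(|Z₁| ≤ 1.96 and |Z₂| ≤ 1.96).
- t = 0.25: 0.091
- t = 0.50: 0.083
- t = 0.75: 0.073
- Three looks, at 0.50, 0.75 and 1: about 0.097

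**4. Type I error, several visits.** Illustrative scenario: the look stops on any of the 2-, 4- or 12-week comparisons (16, 14 and 8 per arm) at p<0.05, and the final test is at 24 weeks with 35 per arm. In simulated null trials the overall error is about 0.17 with within-patient correlation 0.5 and about 0.16 with correlation 0.7. Repeat runs ranged from 0.15 to 0.17.

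**5. A strict interim boundary.** With p<0.001 (|Z| > 3.29) at t = 0.50 and 0.05 at the end, the same formula gives 0.0502.

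**6. Timing if 35 patients must have 24-week data.** H + 24 = 45.7 or 50.1 weeks, against the end of recruitment at 43.5 or 52.2 weeks.

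**The case against.** A reader might infer that the protocol prescribes an unadjusted p<0.05 test at half recruitment, so that its false-positive rate definitely exceeds 5%. The document does not support that. The interim section states no level. The 5% comes from the sample-size reasoning, and a boundary may stand in an analysis plan that is not shown. The word significant is undefined and could be meant clinically. The absence of an alpha adjustment is therefore not a finding in itself, and the error rates above are conditional.

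The remark about CRYO also allows a protective reading, in which the stop operates only if the new technique does badly. With a one-directional interim stop at the same threshold, the overall error at t = 0.50 is 6.7% rather than 8.3%. The 16–17% figure depends on a constructed scenario. If the stop also required the 2-point NPRS difference that Statistical methods treats as clinically important (assumed SD 2.5), the same simulation gives about 12–13%. The 8.3% assumes half the information on the tested endpoint, which at this trigger is near the truth for early visits and not for 24 weeks.

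On timing, half is a minimum. A look at the end of recruitment would have about 31–38 of 70 patients with 24-week scores. If recruitment took 24 months, about 19 of the first 35 would have them.

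These points limit the size of the problem but do not remove it. The trigger and the outcome-based ground are both fixed in this document, the latter listed separately from serious complications. An analysis plan could add a boundary, but it would not by itself make the data mature at a recruitment-based look. If the word significant is not statistical, the outcome-based ground has no criterion here at all.

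**Conclusion.** The point holds in this form: a recruitment-triggered look is combined with an undefined outcome-based reason to stop. Under even accrual over 10–12 months and a look at the 35th patient, at most about 3 of 35 patients would have the 24-week score, and roughly half or fewer the 12-week score (15–19). A stop on outcomes would rest mainly on 2- and 4-week pain.

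The effect on type I error is conditional. It is about 8.3% if one endpoint is tested at 5% both at half information and at the end, less if the stop works in one direction only, and more if several visits can trigger it (about 16–17% in one illustrative scenario). The immaturity of the data depends only on the accrual and timing assumptions, not on how the word significant is read.

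**What to change.** Make the recruitment-triggered interim look safety-only, and delete differences in clinical outcomes as a reason to stop. This needs no new trigger.

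If an outcome-based stop is kept, restrict it to one named between-group NPRS contrast at p<0.001, keep the final test at 0.05 (overall alpha about 0.0502), and base it on patients who have been followed to the named visit. State the consequence openly: if that visit is 24 weeks and 35 patients are required, the look comes at about week 46–50, when recruitment is complete or nearly so, and it can then do little to limit enrolment.

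The edit is a few sentences. The cost is that early stopping for an outcome difference becomes harder under the second option and is given up under the first. Because the final test stays at 0.05, final power is essentially unchanged.
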